### Proposed Therapeutic Protocol

The investigators are proposing a new, noninvasive therapeutic model using tACS to augment CBTp efficacy in individuals with schizophrenia. By selecting electroencephalogram (EEG) brain oscillation activity as a biomarker for the progression of cognitive deficits in schizophrenia, this research seeks to determine whether addressing oscillation perturbations can mitigate cognitive deficits. The heart rate variability (HRV) was selected as a biomarker of improvement of somatic and mental health. The investigators are also aiming for an analysis through a Gender-Based Analysis Plus lens by using the Bem Sex-Role Inventory (BSRI), along with specific tests for psychosis (Positive and Negative Syndrome Scale [PANSS], 16-item Negative Symptom Assessment [NSA-16], etc).

### Objectives

This study compares the effects of a harmless, low-voltage electrical stimulation (tACS) with placebo stimulation (sham tACS) applied for 20 minutes at the beginning of the CBTp session to increase the efficacy of psychotherapy in people living with schizophrenia.

Primary objectives are to determine whether (1) the new intervention protocol using tACS will enhance the EEG activity, expecting that CBTp will enhance EEG activity in clients with schizophrenia at the end of therapy for both groups, with a better outcome for the group with active tACS stimulation; and (2) tACS applied at the beginning of the CBTp sessions in people with schizophrenia will predict better responses to therapy (compared with the sham tACS/CBTp). CBTp is expected to improve the scores of the PANSS, NSA-16, and Cognitive Flexibility Scale (CFS).

The secondary objectives are to determine whether (1) there will be an improvement of level of functioning and quality of life in both intervention groups, with a superior outcome for the group receiving tACS intervention (psychological and psychosocial tests); (2) higher in-session HRV predicts a better response to CBTp (the expectation is that baseline HRV will predict symptom improvement and increase over the course of therapy); and (3) the response to tACS/CBTp intervention is gender specific; considering that cognitive and emotional status is gender dependent, we expect that the therapeutic response could be gender specific.

## Methods

### Trial Design

#### Description

This is a prospective, randomized, repeated-measures, single-blind study design. Preintervention, eligible participants will be randomly assigned to one of two treatment arms: arm 1 (tACS/CBTp, n=14) or arm 2 (sham tACS/CBTp, n=14; tACS is sham, but CBTp is active). In the intervention (16 weeks), participants in arms 1 and 2 will receive once-weekly tACS/CBTp or sham tACS/CBTp. Individuals with schizophrenia (*DSM-5* [*Diagnostic and Statistical Manual for Mental Disorders* {Fifth Edition} criteria) stratified by age and sex. The investigators expect 150 potentially eligible patients from Providence Care Mental Health Services, with 33-40 participants consenting to participate and 28 participants undergoing the research activities (see Figure 1).

Participants will be randomized 1:1 to one of two arms and stratified by age (18-30, 31-55, and >60 years) and by sex (male or female).

**Figure 1 figure1:**
[figure not shown]
CONSORT (Consolidated Standards of Reporting Trials) flow diagram.

#### CBTp Intervention

Participants on both arms will receive CBTp in 16 individual-based, 50-minute-long, weekly sessions with 2 booster CBTp sessions (with active or sham tACS) at 1-month and 3-month follow-up visits (after intervention).

#### tACS/Sham tACS

Participants randomized to the tACS arm will receive gamma band electric stimulation for 20 minutes at the beginning of each CBTp session. After the first 20 minutes of brain stimulation, the tACS device automatically stops, and the device remains in place while the CBTp session continues to run for 30 more minutes.

Participants randomized to the sham tACS arm will receive sham tACS for 20 minutes at the beginning of each CBTp session. After the first 20 minutes of sham tACS, the device automatically stops, and it remains in place, while the CBTp session continues to run for 30 more minutes.

### Selection and Withdrawal of Participants

#### Inclusion and Exclusion Criteria

The inclusion and exclusion criteria for the study participants are listed in Textbox 1.

Changes in medication/new hospitalization for worsening symptoms and/or presence of suicidal ideation are no more exclusion criteria for participants that have passed visit 5 (end of intervention, during follow-up stage); however, the results of the follow-up visits will count at the final results, depending on the severity/imminent danger of symptoms and medication changes, at the best judgment of the principal investigator (FI).

Inclusion and exclusion criteria.

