#### Criteria for Withdrawal

Premature withdrawal or suspension may occur if imminent safety concerns are disclosed to a study team member or a member of the CBTp Clinic by the participant. Withdrawal would be considered with the best interests and safety of the participant considered foremost. An example of this would be if a participant indicated suicidal or homicidal ideation with a plan to carry out such an act at any point in time. After safety considerations are met, the participant would be eligible to return or be included in the study. The research team may temporarily or permanently halt the study if there is any reason to believe that a participant has a medical reason to discontinue participation. Some of the reasons why this might happen are listed below:

Their condition worsens or does not improve, and their doctor thinks they need a different treatment.The study treatment or procedures are found to be unsafe or ineffective.They are unable to follow instructions given to them about the study, or they otherwise cannot do or continue to do what they need to participate in the study.They develop another serious disease.They become pregnant.Cancellation by the sponsor or for other unforeseen reasons that make it necessary to stop their study participation.

If a participant is removed from the study, the study doctor will explain to them why the participant was removed. A participant may also be temporarily suspended or stop their participation in the study if they require attention due to a risk of harm to themselves or others. This may be indicated by a member in their circle of care or by the clinician-researchers on the team. In the event there is a risk of harm to themselves or others, after the risk is no longer deemed significant, they may be able to continue the study.

If participants who have passed visit 5 (end of intervention, during the follow-up stage) and do not withdraw their consent to participate, their data can be considered for use.

Participant withdrawal forms have been created to accurately document any withdrawal.

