### Enrollment and Randomization

After the screening visit, participants will be randomized in a 1:1 ratio with stratification according to age and sex.

Maintaining the blind is covered by the device, which induces a discrete tickling sensation at the starting point of the intervention for participants on sham tACS. This study is single blind, being blinded only for participants. In case of emergency, the research team would be aware of the interventional (or sham) nature of the problem. Communication with participants regarding this aspect will be possible only at the end of the study, at the end of visit 6 (second follow-up), at the patient’s request, or after they withdraw from the study. At the study closure, each participant will receive a debriefing letter containing unblinding disclosure.

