### Statistical Outcomes

#### Primary Outcome Measures

EEG gamma oscillations are fast neural rhythms linked to higher-order cognitive functions (attention, working memory, executive control, and consciousness). In the prefrontal cortex, gamma EEG activity is associated with working memory maintenance, cognitive flexibility, top-down attention control, and integrating information across cortical areas. Altered prefrontal gamma observed in schizophrenia. EEG measurement of gamma activity in the prefrontal cortex refers to detecting brain oscillations in the gamma frequency band (typically 30-100 Hz, often subdivided into low gamma: 30-50 Hz, and high gamma: 60-100 Hz) from scalp electrodes positioned over prefrontal areas. In a within-subject design, we will compare gamma power across time windows (pre- and postintervention). In a between-subject design, we use mixed models or *t* tests on summary metrics (mean power in time×freq window).

PANSS is a standardized clinical interview that rates the presence and severity of positive and negative symptoms and general psychopathology for people with schizophrenia within the past week [32]. The scale consists of 30 items: 7 positive, 7 negative, and 16 general psychopathology symptoms. The symptom severity for each item is rated according to a 7-point scale (1=absent to 7=extreme) to best describe the symptom’s presentation. The clinical interview takes approximately 45 minutes. The patient is rated from 1 to 7 on 30 different symptoms based on the discussion and reports of family members or primary care hospital workers. As 1 is the lowest score for each item, a patient cannot score lower than 30 for the total PANSS score. Scores are often given separately for positive items, negative items, and general psychopathology. [Time frame: PANSS will be applied at visit 1, screening (week 0); visit 4, end of intervention (week 17); visit 5, follow-up 1 (week 21); and visit 6, follow-up 2 (week 29).]

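### An investigator not blinded to arm decides which follow-up results count, according to symptom severity and medication change, and the visit that marks the cut-off is contradictory

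*Protocol article*

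**What the plan says.** All references are to the protocol article.

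- **Which results count.** Under Inclusion and Exclusion Criteria: "Changes in medication/new hospitalization for worsening symptoms and/or presence of suicidal ideation are no more exclusion criteria for participants that have passed visit 5". For these participants "the results of the follow-up visits will count at the final results, depending on the severity/imminent danger of symptoms and medication changes". The decision is made "at the best judgment of the principal investigator", and no criterion for it is given.
- **The same events as exclusions.** The exclusion list includes "Changes in medication/new hospitalization for worsening symptoms and/or presence of suicidal ideation".
- **Withdrawal.** Criteria for Withdrawal gives, among the reasons why participation might be stopped, "Their condition worsens or does not improve, and their doctor thinks they need a different treatment". A later sentence begins "If participants who have passed visit 5 (end of intervention, during the follow-up stage" and says that the data of those who keep their consent may be considered.
- **Blinding.** Under Enrollment and Randomization: "This study is single blind, being blinded only for participants".
- **Visit numbering.** The PANSS time frame under Primary Outcome Measures reads "visit 4, end of intervention (week 17". It places visit 5 at week 21 as the first follow-up. NSA-16, CFS and Table 2 agree with it.
- **Purpose.** Statistical Considerations: Sample Size says that the pilot should estimate the SD and preliminary effect size of the primary outcome without bias, so that a later trial can be sized. It also calls the outcome analyses descriptive.

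**The concern.** Worsening symptoms and a change of antipsychotic after randomisation are close to being the outcome itself. A rule that counts or discounts follow-up results according to these events selects data on the outcome. Because only participants are blinded and no criterion is fixed, the selection can also differ between arms without anyone intending it.

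Two products of the pilot are exposed. The between-arm effect estimate is biased if removal differs by arm. The SD is understated whenever poor outcomes are removed, even if removal is equal, and that SD is meant to size the next trial.

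The wording also suggests a wider effect. If the listed events cease to be exclusions only after visit 5, they presumably apply to randomised participants before it. Whether such a participant's earlier data then leave the analysis is not stated.

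**Working it through.** **1. The reach of the clause.** It covers follow-up results, so PANSS, NSA-16 and CFS at weeks 21 and 29 are affected. The Abstract names both follow-ups as times at which the primary outcomes are evaluated. By Table 2, EEG is taken only at visits 1 and 4, and the responder definition uses the end of the intervention, so the clause touches neither of these.

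**2. The cut-off.** Two sections attach the label of end of intervention to visit 5. The outcome time frames and Table 2 attach it to visit 4 (week 17), with visit 5 at week 21. The gap is 21 − 17 = 4 weeks. If the label governs, both follow-ups come after the cut-off. If the visit number governs, the exclusions still apply between weeks 17 and 21, and only visit 6 remains to be judged.

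**3. The plan's own figure.** With 14 per arm, a two-sample t test, two-sided 5% level and 80% power (both assumed, as the article states neither), the minimal detectable d is 1.10. The article's value of about 1.1 is reproduced.

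**4. Illustration of bias in the difference.** Assumptions: no true effect, SD 1, 14 per arm before dropping, and drop counts taken from the article's 15%-20% attrition (14 × 0.15 = 2.1; 14 × 0.20 = 2.8, so 2 or 3, with 1 added as a mild case). Simulated results, 40,000 trials per scenario, dropping from one arm only:

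| Dropped from one arm | Worst outcomes dropped | Dropping correlates 0.6 with outcome |
|---|---|---|
| 1 | 0.13 SD | 0.08 SD |
| 2 | 0.24 SD | 0.15 SD |
| 3 | 0.34 SD | 0.21 SD |

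A closed form confirms this. The three lowest of 14 standard normal values have expectations −1.704, −1.208 and −0.901, so removing k of them raises the mean by their absolute sum divided by (14 − k):

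- k = 1: 1.704/13 = 0.131
- k = 2: 2.912/12 = 0.243
- k = 3: 3.813/11 = 0.347

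The simulation agrees within 0.004. Multiplying by 0.6 gives 0.079, 0.146 and 0.208. Dropping 3 in one arm and 1 in the other gives 0.13 to 0.22 SD. With nobody dropped, the bias is 0.00.

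**5. Equal dropping in both arms.** With 2 or 3 dropped per arm the difference is unbiased, but each arm's mean improvement rises by 0.15 to 0.35 SD.

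**6. Effect on the SD.** For a normal outcome with the lowest fraction p removed at cut point z, let λ = φ(z)/(1 − p). The remaining variance is 1 + zλ − λ².

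- p = 0.15: z = −1.036, λ = 0.274; variance 1 − 0.284 − 0.075 = 0.64, SD 0.80.
- p = 0.20: z = −0.842, λ = 0.350; variance 1 − 0.295 − 0.122 = 0.58, SD 0.76.

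With correlation 0.6 the variance is 1 − 0.36 × (1 − the value above), that is 0.87 and 0.85 (SD 0.93 and 0.92). For a fixed raw difference, sample size is proportional to the variance. A later trial sized on these figures would be too small by 36% to 42% in the extreme case, and by 13% to 15% in the milder one.

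**The case against.** The strongest reply is that this is a descriptive pilot not powered for efficacy, that the clause reaches only two follow-up visits, and that the article reports little attrition so far. Of 15 enrolled, 2 were screening failures and 1 withdrew, so 1/13, about 8%, with arm and reason not given. The descriptive status does make false-positive rates a poor measure of harm, which is why the sizes here are given for the effect and the SD. It does not protect those estimates, which are the pilot's stated product. The limited reach stands and rules out any claim that the whole randomised comparison is lost.

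A reader might infer four stronger points that the article does not support:

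- **That only data from participants past visit 5 are usable.** The article says that such data may be considered, not that earlier data of others are discarded. The Pregnancy section keeps recording standard-of-care data after withdrawal, and suspended participants may return. Removal of earlier data is plausible from the wording but not stated.
- **That lack of improvement alone leads to withdrawal.** The reason also requires the doctor's view that a different treatment is needed, and the list is permissive. Minor medication adjustments are allowed.
- **That the same unblinded team rates PANSS and NSA-16.** Blinding only participants means that no blinded rating is described, but the raters are not named.
- **That a particular bias will occur.** The drop counts are assumptions, and dropping exactly the worst outcomes is the extreme case. Equal dropping leaves the difference unbiased.

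The definition of the analysis set may properly sit in an SAP. This clause, however, is a rule that the protocol itself fixes.

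**Conclusion.** The point holds in this form: week 21 and week 29 results count at the discretion of an investigator who is not blinded, according to events closely tied to the outcome, and the visit from which this applies is contradictory by four weeks. It conflicts with the aim of unbiased estimates and should be corrected before analysis.

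Neither the size nor the direction of any bias follows from the documents. Under the stated assumptions, one-sided dropping of 1 to 3 of 14 gives 0.08 to 0.34 SD of spurious difference, depending on how closely dropping follows the outcome. Removing the worst 15%-20% understates the SD by about 7% to 24%. Loss of data from before visit 5 is a plausible reading that the sponsor should settle.

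**What to change.** - Delete the clause that leaves the counting of follow-up results to the investigator's judgement.
- State that all randomised participants are analysed in their assigned arm, using all data collected to week 29 regardless of medication change, hospitalisation, suicidal ideation or stopping the intervention, unless consent to use the data is withdrawn.
- Distinguish stopping the intervention from leaving the study, and keep the scheduled assessments for those who stop and agree to attend.
- Add one prespecified sensitivity analysis that sets data to missing after a significant antipsychotic change, with that term defined in advance. It needs a model that accepts incomplete records, because a standard repeated-measures ANOVA would drop the whole participant.
- Reconcile visit 4 with visit 5 wherever the end of the intervention is named.

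The clinical rules for stopping treatment are not touched. The cost is an amendment to protocol and SAP wording while enrolment is under way, plus the effort of keeping assessments for those who stop. The sample size does not change. The small downside is that the estimates will include participants with medication changes and may look less favourable.

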**Inclusion criteria**
Individuals, with at least 5 years’ duration of illness, who meet diagnostic criteria for schizophrenia according to the *Diagnostic and Statistical Manual for Mental Disorders* (Fifth Edition) and at least one residual positive symptom (as determined by the referring physician)No change in medication regimen for at least 1 month, preferably 3 months (minor dose adjustments and/or change in medication involving symptoms, such as sleep, anxiety, or medical symptoms such as fever and pain, are permitted)All genders between ages 18-65 years; participants >65 years may be eligible if cognition assessed by the Montreal Cognitive Assessment score is greater than or equal to 26Ability to understand English with a reading level at or above grade 6Able to understand and comply with the requirements of the studyProvision of written informed consent
**Exclusion criteria**
Current drug substance useCurrent suicidal ideation/planCurrent enrollment in cognitive behavioral therapy for psychosis or other formalized psychosocial interventionsUndergone vagotomy or surgery on the vagus nerveComorbid neurological condition, including seizuresCurrent fibrillation or pacemakerSevere or moderate intellectual disabilityCurrently undergoing hormone therapyUnder 18 years of ageChanges in medication/new hospitalization for worsening symptoms and/or presence of suicidal ideation

#### Criteria for Withdrawal

Premature withdrawal or suspension may occur if imminent safety concerns are disclosed to a study team member or a member of the CBTp Clinic by the participant. Withdrawal would be considered with the best interests and safety of the participant considered foremost. An example of this would be if a participant indicated suicidal or homicidal ideation with a plan to carry out such an act at any point in time. After safety considerations are met, the participant would be eligible to return or be included in the study. The research team may temporarily or permanently halt the study if there is any reason to believe that a participant has a medical reason to discontinue participation. Some of the reasons why this might happen are listed below:

Their condition worsens or does not improve, and their doctor thinks they need a different treatment.The study treatment or procedures are found to be unsafe or ineffective.They are unable to follow instructions given to them about the study, or they otherwise cannot do or continue to do what they need to participate in the study.They develop another serious disease.They become pregnant.Cancellation by the sponsor or for other unforeseen reasons that make it necessary to stop their study participation.

If a participant is removed from the study, the study doctor will explain to them why the participant was removed. A participant may also be temporarily suspended or stop their participation in the study if they require attention due to a risk of harm to themselves or others. This may be indicated by a member in their circle of care or by the clinician-researchers on the team. In the event there is a risk of harm to themselves or others, after the risk is no longer deemed significant, they may be able to continue the study.

If participants who have passed visit 5 (end of intervention, during the follow-up stage) and do not withdraw their consent to participate, their data can be considered for use.

Participant withdrawal forms have been created to accurately document any withdrawal.

#### Inclusion of Women and Minorities

Our project is gender and minority inclusive. All participants included will have a diagnosed mental health disorder of schizophrenia. The investigators plan to include individuals who are both inpatients and outpatients at Providence Care Hospital. This includes participants who may be in long-term care.

#### Disability

Individuals will be excluded if they have severe or moderate intellectual disability or dual diagnosis due to the nature of CBTp, which requires the learning of coping strategies, adequate attention and memory, engagement using speech, and appreciation of consequences of action, thoughts, behaviors, emotions, and beliefs, which are limited in severe intellectual disability.

#### Language and Linguistic Proficiency

Individuals will be excluded if they cannot understand English with a reading level at or above grade 6. The ability for an individual to meaningfully engage in a CBTp talk therapy would be limited if their English level is limited to a grade 6 level and is not thought to be substantially beneficial to the individual.

#### Age

Participants recruited will be included if they are aged 18-65 years. Individuals older than 65 years of age will be required to be assessed by the Montreal Cognitive Assessment (MoCA) and will be included in the study if results validate adequate cognitive performance. The MoCA will be administered at the screening stage (a score under 26 will be the exclusion criterion).

